### Allocation

#### Sequence generation

Participants will be individually randomised 1:1 to the BCT or the control arm (Befriending). A randomly permuted block randomisation list will be computer-generated by an independent statistician, stratified by site (ie, Austin, Alfred, RMH, SVHM or Christchurch) and hyperventilation symptoms (baseline Nijmegen score >23 vs ≤23).

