Box 1OutcomesPrimarySeizure remission, defined as seizure frequency of zero in the preceding 4 weeks (recorded by the participant in a seizure frequency diary), measured at Week 12 (12 weeks post the initial treatment session).SecondaryChanges in hyperventilation from baseline, measured by the Nijmegen scale of hyperventilation provided at baseline, Week 4, Week 12 and Week 24.Changes in healthcare utilisation from baseline, measured via a tailored resource use questionnaire provided at baseline, Week 12 and Week 24, as well as changes in health service use ascertained from Services Australia and CVDL data (Services Australia and CVDL data for consenting participants only).Changes in quality of life from baseline, measured by the Assessment of Quality of Life Eight Dimension provided at baseline, Week 4, Week 12 and Week 24.Changes in depression and anxiety symptoms from baseline, measured by the 9-item Patient Health Questionnaire and Generalised Anxiety Disorder Assessment respectively, provided at baseline, Week 4, Week 12 and Week 24.Changes in occupational and social functioning from baseline, measured by the Work and Social Adjustment Scale provided at baseline, Week 4, Week 12 and Week 24.Acceptability of BCT captured by a tailored self-report questionnaire provided after attending the Week 4 ‘booster’ session.Safety of BCT assessed by the occurrence of adverse events reviewed at Week 4, Week 12 and Week 24.tcCO_2_ levels (mm Hg; a marker of hyperventilation) preceding or during seizures, BPAT score (at baseline) and/or Nijmegen score (at baseline), to predict response to treatment.ExploratoryThe presence of significant life events in childhood and adolescence (≤16 years of age), and 12 months preceding the onset of their FS, assessed via the Childhood Experience of Care and Abuse Questionnaire and the LEDS*, respectively, to gauge moderators of treatment response.The MDI and Toronto Alexithymia Scale provided at baseline will be assessed if predictors of treatment response. MDI scores at Week 4, Week 12 and Week 24 will be assessed if they correlate with treatment response.*Note, the LEDS is optional, and only relevant to participants whose FS have started within the last 2 years.BCT, breathing control training; BPAT, Brompton Breathing Pattern Assessment Tool; CVDL, Centre for Victorian Data Linkage; FS, functional seizures; LEDS, Life Events and Difficulties Schedule; MDI, Multiscale Dissociation Inventory; tcCO_2_, transcutaneous carbon dioxide.

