#### Implementation

After prescreening and eligibility for the trial confirmed, and baseline self-report questionnaires completed (to obtain Nijmegen score for stratification purposes), the physiotherapist will contact the participant and inform them of their group allocation (randomisation) according to the randomisation allocation provided by REDCap.

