##### Nijmegen scale of hyperventilation

A 16 item, self-reported questionnaire which explores symptoms associated with dysfunctional breathing patterns, introduced over 35 years ago as a screening tool to detect patients with hyperventilation problems. Each item is answered by the participant on a 5-point Likert scale ranging from ‘never’ (equating to zero) to ‘very often’ (equating to four points). Total scores range from 0 to 64, with a score of over 19 indicating the presence of respiratory distress and dysfunction. The Nijmegen scale is estimated to take 2–3 minutes to complete.^33^

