#### Primary outcome

FS remission (table 2) will be analysed using a random intercept logistic regression model, including in the model factors visit, study group, visit by study group interaction and the stratification factors. This model will be further adjusted for FS frequency at baseline. The relative and absolute treatment effect estimate and corresponding two-sided 95% CI, and p value of BCT compared with Befriending at Week 12 will be obtained to evaluate the primary hypothesis. In addition, an adjusted treatment effect will be obtained by including potential covariate (eg, depression) in the model.

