## Discussion

This study described the design and methodology of the first multicentre, randomised, assessor-blinded, two-arm, parallel-group efficacy and acceptability trial of BCT versus control in patients with FS. Despite increased research in interventions for FS, and an abundance of smaller studies suggestive of therapeutic effect, there remain no definitive, validated treatments.^10^ Once completed, this study will represent only the second appropriately powered, multicentre, randomised trial of an intervention for FS.^22^ We hypothesise that BCT will reduce the seizures and related symptoms of FS greater than a control intervention designed to provide no benefit.

BCT has been found to be safe and well-tolerated when provided to people with respiratory conditions.^25^ As a brief intervention, it should prove cheap to deliver, and as an allied health intervention, it may prove more acceptable than psychotherapy interventions, where large proportions will not participate or complete the intervention.^22^ Its efficacy in FS remains to be determined, as it has not been subject to a trial other than our own pilot.^17^

The mechanism of any effect remains to be determined, but the therapy was designed to address abnormal breathing patterns, particularly hyperventilation, and in our pilot study, improvement correlated with improvement in this. People with FS do commonly have abnormal breathing, not only around the time of their FS.^13^ There are a priori reasons to think the intervention may work in FS, in the same way that it has worked in asthma. A goal of this study is to explore the mechanism of any effect, particularly in regard to breathing pattern, whether measured by clinical observation of breathing patterns, questionnaires or CO_2_ measurements. If the intervention is only effective in a subgroup defined by its breathing pattern, we would hope to be able to identify it.

The large sample size and randomised placebo-controlled design are significant methodological strengths in the current study. A further strength is the assessment of clinical outcomes at prolonged follow-up. Previous clinical trials have produced impressive results at the end of the intervention, only for a substantial proportion to relapse in follow-up.^10^ A final advantage for this study is the heterogeneity of the sample. The broad inclusion and limited exclusion criteria mean that participants experiencing a range of psychiatric comorbidities will be eligible.

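### The primary model uses baseline Nijmegen only as the >23 / ≤23 randomisation stratum; adding the continuous score, already collected, would be a small and cheap improvement

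*Protocol article*

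**What the plan says.** The Sequence generation section stratifies the 1:1 block randomisation by site and "hyperventilation symptoms (baseline Nijmegen score >23 vs ≤23". The Implementation section has the baseline questionnaires completed before allocation, "to obtain Nijmegen score for stratification purposes", so every randomised participant has a full score. The Nijmegen section gives its scale: "Total scores range from 0 to 64".

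Under Statistical analysis, Primary outcome, remission is analysed by random-intercept logistic regression "including in the model factors visit, study group, visit by study group interaction and the stratification factors", further adjusted for baseline seizure frequency. An additional adjusted estimate may include other covariates, with depression as the example. Continuous Nijmegen is not named in either model.

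Separately, Box 1 lists as a secondary outcome the baseline "Nijmegen score (at baseline), to predict response to treatment", with no cut-off.

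**The concern.** Hyperventilation is the proposed mechanism, and the Nijmegen score is the hyperventilation measure that everyone has at baseline; tcCO2 exists only for those routinely monitored. The Background reports that in the pilot, seizure frequency correlated with Nijmegen score (Spearman 0.75, with 10 of 18 participants completing follow-up). A variable the investigators expect to be related to seizures is a natural candidate for covariate adjustment.

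Once reduced to two levels, the model treats a participant scoring 24 like one scoring 60, and one scoring 23 like one scoring 2. Whatever prognostic information lies within the strata is left in the residual variation. What is at stake is some efficiency in the Week 12 comparison, and nothing about its validity.

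**Working it through.** **1. The plan's own figure.** Inputs from the sample size section: remission 40% v 20%, two-sided 5%, 80% power, 25% drop-out. With pooled variance and no continuity correction,

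n per arm = [1.960·√(2·0.3·0.7) + 0.842·√(0.4·0.6 + 0.2·0.8)]² / 0.2² = (1.270 + 0.532)² / 0.04 ≈ 81.2, rounded up to 82.

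82 / 0.75 = 109.3, rounded up to 110 per arm, so 220 in total. This matches the article. Neither Nijmegen nor any covariate enters the calculation, so a change to the adjustment set leaves it untouched.

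**2. What the model contains.** Named terms: visit, study group, their interaction, site, the Nijmegen stratum and baseline seizure frequency. The 0 to 64 score appears only through its stratum.

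**3. How much of the score the stratum carries.** The article gives no mean or SD, so this step rests on an assumption: normal scores, mean 20, 25 or 30, SD 10, 12 or 14. With z = (23.5 − mean)/SD and q = P(score > 23), the correlation of the >23 indicator with the score is r = φ(z)/√(q(1−q)).

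| Mean | SD | z | q | φ(z) | r | r² |
|---|---|---|---|---|---|---|
| 25 | 12 | −0.125 | 0.550 | 0.396 | 0.80 | 0.63 |
| 30 | 10 | −0.650 | 0.742 | 0.323 | 0.74 | 0.55 |

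Over all nine combinations r runs from 0.74 to 0.80 and r² from about 0.55 to 0.63. Roughly 37% to 45% of the score's variance (1 − 0.63 to 1 − 0.55) then lies within strata and is unused.

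**4. What that figure is not.** It is the share of variance in the covariate. It is not a loss of power and not a bias in the treatment effect. Turning it into a gain would require knowing how strongly baseline Nijmegen predicts Week 12 remission once baseline seizure frequency is in the model, and the article does not say.

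**5. The two cut-offs.** The Nijmegen section describes the instrument "with a score of over 19 indicating the presence of respiratory distress and dysfunction". Integer scores above 19 that fall in the ≤23 stratum are 20, 21, 22 and 23. Nothing in eligibility, randomisation or the analysis section refers to 19.

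**The case against.** **Adjusting for the strata as randomised is standard.** It is, and leaving out the continuous score is not a mistake. This stands, so the point is a suggested improvement.

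**The further adjusted model, or the SAP, may include it.** Possibly. But the further model is additional to the primary one and names only depression. The primary model is set out in the article term by term, so this concerns a stated choice that can still be amended while the SAP is being written.

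**The evidence that the score is prognostic is thin.** This also stands. The pilot correlation rests on at most 10 completers, and the Discussion describes it as improvement tracking improvement, which is not the same as baseline score predicting later remission. Baseline seizure frequency is already adjusted for and may carry part of the same information. Hence a modest expected gain.

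**A stronger reading that the documents do not support.** A reader might infer that the thresholds 19 and 23 contradict each other, so that participants scoring 20 to 23 are misclassified, or that a responder subgroup could be defined at whichever threshold looks better. The over-19 figure is a general description of the instrument. A stratification cut need not equal a screening threshold, and the article does not call the ≤23 stratum free of dysfunction. Box 1 names the score as predictor without any cut-off. The Discussion's remark, "If the intervention is only effective in a subgroup defined by its breathing pattern, we would hope to be able to identify it", follows a sentence that also lists clinical observation and CO2 measurement; it expresses a hope and specifies no Nijmegen split. The form of any interaction or subgroup analysis properly belongs in the SAP, which is to be written before unblinding.

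**Conclusion.** The primary model carries baseline Nijmegen only as a two-level stratum, although the full score is available for every randomised participant and there is some reason to expect it to be prognostic. Adding it is worthwhile but minor. The comparison as planned is valid, and type I error, the stated power and N=220 do not depend on this.

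The only size that can be given is conditional: about 55% to 63% of the score's variance is retained by the stratum if scores are normal with mean 20 to 30 and SD 10 to 14. The effect on the precision of the Week 12 comparison cannot be computed from the article and is probably modest. The difference between 19 and 23 is not an error.

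**What to change.** Leave randomisation as it is; recruitment began in February 2024. Keep the >23 / ≤23 stratum in the primary model, and add the continuous baseline Nijmegen score beside it, with its form (linear or spline) fixed in the SAP before unblinding. The cost is one parameter if linear or a few if spline, plus an assumed functional form that can be checked. It needs no new data and no change to the sample size.

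Optionally, add one sentence saying why 23 was chosen for stratification when the instrument is described with a threshold of 19.

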#### Allocation concealment mechanism

Participants will be allocated sequentially following the randomisation schedule. The randomisation schedule will be stored by an independent statistician, as well as on REDCap, with access only permitted to the physiotherapists (who are unblinded during the trial).

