### Consent

Participants may be consented into the trial by the referring clinician, the RA or the physiotherapist, who will follow the standard operating procedure for informed consent specific to the participant’s clinical care site. All participants will need to provide written informed consent prior to commencing the study and data collection occurring (excluding data obtained on the prescreening questionnaire used to determine eligibility). Participants may consent via (1) a hard-copy, site-specific consent form (see online supplemental material) or (2) electronically via REDCap. The latter will allow participants who are discharged from their clinical care site to consent to the study from home at their convenience. Participants below the age of 18 will be required to discuss the trial with their parent/guardian and both the young person and parent/guardian will be required to co-sign the consent form. After first receiving the consent form, the candidate may have as long as they wish to consider proceeding with the trial (while recruitment for the project is open).

For Australian participants, consent will be sought to access data on use of healthcare services through MBS and PBS. A specific consent form, following guidelines from Services Australia, will be provided for this (optional) component. In addition, Victorian participants will be asked to provide consent on their site-specific consent form to enable CVDL data retrieval. Participants will also be asked to provide extended consent for their non-identifiable data to be used in future projects closely related to this project, or in the same general area (as per the NHMRC National Statement, 2018). If significant changes to the study design occur, all participants will be contacted and asked to review an amended consent form outlining these changes, allowing them to re-negotiate their consent.

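### As worded, the concealment rule does not stop a physiotherapist who takes consent from knowing upcoming assignments

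*Protocol article*

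**What the plan says.** Four sections of the protocol article bear on this point.

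- **Sequence generation.** "A randomly permuted block randomisation list will be computer-generated by an independent statistician". It is stratified by the five sites and by baseline Nijmegen score (above 23, or 23 and below). The article gives no block size.
- **Allocation concealment mechanism.** "Participants will be allocated sequentially following the randomisation schedule". On custody: "The randomisation schedule will be stored by an independent statistician, as well as on REDCap, with access only permitted to the physiotherapists". A parenthesis adds that the physiotherapists are unblinded during the trial.
- **Implementation.** Once eligibility is confirmed and the baseline questionnaires are complete, "the physiotherapist will contact the participant and inform them of their group allocation (randomisation) according to the randomisation allocation provided by REDCap".
- **Consent.** "Participants may be consented into the trial by the referring clinician, the RA or the physiotherapist".

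The section on Befriending adds that the same physiotherapists deliver the control sessions.

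**The concern.** Concealment means that whoever decides if and when a person enters the trial cannot know what that person will be allocated. The concealment section gives access to the schedule itself, not to assignments already issued, and it gives that access to a group that the Consent section allows to enrol. Nothing in the article separates the two roles or restricts what the access shows.

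If upcoming assignments can be seen, the choice of whom to consent, and when, can depend on the next arm. That selection happens before randomisation, so analysis by intention to treat does not protect against it. The primary model adjusts for the stratification factors and baseline seizure frequency, and a further analysis adds covariates such as depression. This may absorb part of an imbalance, but it may not fully remove selection on unrecorded features such as motivation or expected response. Participants and therapists are not blinded and the primary outcome comes from a participant diary, so concealment is one of the few protections this design can have in full.

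**Working it through.** **1. The access and enrolment rules side by side.** Schedule access: the independent statistician who stores it, and the physiotherapists. Permission to consent: referring clinician, research assistant, physiotherapist. The physiotherapist is on both lists. No section says that access begins only after a participant is committed, or that it covers issued assignments only.

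**2. What foreknowledge would be possible.** Five sites × two Nijmegen levels = 10 lists, so two per site. If the schedule can be read and the stratum is known, the next assignment is certain. For comparison, guessing from past assignments with a known block size would be right about 71%, 68% or 67% of the time for blocks of 4, 6 or 8 (assumed sizes).

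The Nijmegen score is obtained after consent, so at consent the stratum may be unknown. With 1:1 allocation and independently generated lists (assumed), the next slots of a site's two lists name the same arm with probability ½ × ½ + ½ × ½ = ½. In those cases the assignment is known whatever the score turns out to be.

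**3. The planned sample size, reproduced.** Inputs from the sample size section: 40% versus 20%, 80% power, two-sided 5%, 25% drop-out.

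n per arm = [1.96 × √(2 × 0.30 × 0.70) + 0.8416 × √(0.40 × 0.60 + 0.20 × 0.80)]² / 0.20² = (1.270 + 0.532)² / 0.04 ≈ 81.2, rounded up to 82. Then 82 / 0.75 = 109.3, rounded up to 110 per arm and 220 in total. This matches the plan. The concealment wording does not affect it.

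**4. Illustration of the consequence.** Assume no true effect, overall remission of 20% (the plan's Befriending rate), 82 evaluable per arm, and selective enrolment that leaves the BCT arm with a remission prognosis better by s. The arm rates are then 0.20 + s/2 and 0.20 − s/2. For an unadjusted two-proportion test:

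- SE under the null = √(2 × 0.20 × 0.80 / 82) = 0.0625, so the critical difference is 1.96 × 0.0625 = 0.1224.
- SE under the shift = √([p₁(1 − p₁) + p₂(1 − p₂)] / 82).
- Rejection rate = 1 − Φ[(0.1224 − s)/SE] + Φ[(−0.1224 − s)/SE].

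| Assumed gap s | Arm rates | Upper tail | Lower tail | Two-sided error |
|---|---|---|---|---|
| 0 | 20% / 20% | 2.5% | 2.5% | 5.0% |
| 2 points | 21% / 19% | 5.0% | 1.1% | 6.2% |
| 5 points | 22.5% / 17.5% | 12.3% | 0.3% | 12.5% |
| 10 points | 25% / 15% | 35.9% | 0.02% | 35.9% |

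The gaps are assumptions. The article gives no figure from which to estimate one.

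**The case against.** The strongest reply is that the Implementation section describes the working procedure: the physiotherapist acts on an allocation that REDCap provides, after eligibility and baseline are complete. That fits one-at-a-time release. The parenthesis about unblinded physiotherapists can likewise be read as saying who may know allocations once made, as opposed to the blinded research assistant. An article also condenses a fuller protocol, and detailed REDCap user rights may well be set out there. This reply stands to the extent that a reader might infer that the whole schedule is open to the physiotherapists and that allocation is unconcealed. The article does not say what the access displays, so neither follows. What survives is the literal wording of the concealment section, which grants access to the schedule and is not limited anywhere else in the article.

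There are also partial safeguards. Candidates come by referral from the care team or by letter from the site investigator. Diagnosis needs an epileptologist and a captured event on video EEG. The stratum is scored only after consent, and two other roles may take consent. These reduce the opportunity without closing it. There are only two lists per site, candidates may take as long as they like to decide, and the frequency criterion is self-reported, so timing of entry is flexible.

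A reader might also infer that physiotherapists, because they deliver both arms, have a stake in who receives which. Nothing in the article supports a motive, and the point does not need one.

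Finally, a 10-point gap would need strong and sustained steering by one of three consenting roles, and the illustration ignores covariate adjustment. That is fair; the 2-point row shows how small the effect could be.

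**Conclusion.** The concern holds as a defect in the stated mechanism. The concealment and Consent sections together permit a person who enrols to know upcoming assignments, and the one sentence that might imply otherwise does not state a limit. The article does not show that assignments were visible in advance or that enrolment was steered.

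The bias cannot be sized from the document. Under the assumptions above, the false-positive rate would run from about 6% to about 36% for gaps of 2 to 10 points. Covariate adjustment could lower these figures by an unknown amount. It is worth correcting now because selection of this kind cannot be reliably repaired in the analysis, and recruitment, which began in February 2024, is expected to stay open for four years.

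**What to change.** - **Allocation concealment mechanism.** State, and enforce in REDCap, that the schedule is held only by the independent statistician and in the locked randomisation module; that each assignment is released singly once consent, eligibility and the baseline Nijmegen score are saved; and that physiotherapists see only assignments already issued.
- **Implementation and Consent.** Reword both so that they agree with this sequence.
- **Check what has happened so far.** Review the REDCap access rights and log, and report whether future assignments were ever visible to anyone taking consent.
- **If they were visible, or if single release cannot be enforced,** physiotherapists with access should not take consent.

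The cost is a permission setting, a few sentences and one log review. The last, conditional step slightly reduces flexibility in who takes consent. Sample size, outcome and analysis model do not change.
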